**Fig. 1 Fig1:**
[figure not shown]
Standard Protocol Items: Recommendations for Interventional Trial (SPIRIT) Figure, study design overview. *Done by podiatrist during outpatient clinic visit, or retrospectively, from outpatient visit lists. *T*_*3,*_
*T*_*6,*_
*T*_*9*_,…refer to assessments at 3, 6, 9,…months’ follow-up. *PAD* peripheral arterial disease, *SF-36* 36-Item Short Form Health Survey, *EQ-5D-3 L*  3-Level EuroQol Quality of Life Scale, *iPCQ* Medical Technology Assessment (iMTA) Productivity Cost Questionnaire, *iMCQ* iMTA Medical Consumption Questionnaire

### Participants

The study population consists of patients that are at high-risk of developing a foot ulcer. These are diabetic patients with a loss of protective sensation based on peripheral neuropathy and a history of foot ulceration in the 4 years prior to inclusion in the study, or a history of Charcot neuro-osteoarthropathy (IWGDF diabetic foot risk classification category 3 [22]).

### Inclusion and exclusion criteria

In order to be eligible to participate in this study, a participant must meet all of the following inclusion criteria:Diagnosis of diabetes mellitus types 1 or 2Aged 18 years or aboveHave loss of protective sensation based in the presence of peripheral neuropathy [22]Have a recent history of a foot ulcer or foot amputation, i.e., an ulcer, defined as cutaneous erosion through the dermis without reference to time present [22, 23], has been present for at least 2 weeks and has healed within 4 years before randomization; or a confirmed diagnosis of midfoot or forefoot Charcot neuro-osteoarthropathyAbility to provide informed consentAmbulatory status (i.e., not permanently wheel-chair bound)The participant has foot care from a podiatrist or is willing to undergo foot care by a podiatrist

And not have any of the following exclusion criteria:Active foot ulceration or open amputation sitesActive Charcot neuro-osteoarthropathyActive foot infection, based on criteria of the Perfusion, Extent, Depth, Infection, and Sensation (PEDIS) classification [23]Amputation proximal to the Chopart joint in both feetCritical limb ischemia, based on criteria of the PEDIS classification [23]Severe illness that would make 18 months’ survival unlikely, based on the clinical judgment by the physicianConcomitant severe physical or mental condition(s) that limit the ability to follow instructions for the study, based on the clinical judgment by the physician. This includes the inability to perform temperature measurements, without having a caretaker who can perform the temperature measurementsCurrent use of at-home foot temperature monitoring

### Sample size calculation

Based on the results of a footwear efficacy trial that was largely conducted in the same centers as this trial and also assessed patients with a history of foot ulceration [24], we anticipate for the usual-care group that 44% of participants will develop a recurrent foot ulcer during 18 months’ follow-up. Using a conservative estimate from three previous trials on the effectiveness of at-home foot temperature monitoring [15–17], we anticipate that 28.6% of participants in the enhanced therapy group will develop a recurrent foot ulcer in 18 months; this represents a 35% effect size. With α = 0.05 (two-sided), power 80%, and based on an intention-to-treat analysis in which clinical outcome data from all included patients will be assessed, 304 eligible participants are required and will be randomly assigned.

### Randomization and blinding

After the baseline assessment, participants will be randomly assigned to either usual care or enhanced therapy using an online-accessible, computer-generated allocation sequence (TENALEA Clinical Trial Data Management System; National Cancer Institute, Amsterdam, The Netherlands) that uses the nondeterministic minimization method. The allocation sequence will be prepared and managed by a noninvolved investigator from the Clinical Research Unit of the Academic Medical Center in Amsterdam. Randomization will be stratified according to participating center and gender.

The persons responsible for assessing the primary clinical outcome (i.e., foot ulcer) will be blinded to the group allocation. Participants are asked not to disclose their allocation in the study to their treating physician. The involved podiatrists and investigators are not blinded to group allocation.

### Usual care

Usual care as provided in the Netherlands generally follows universal guidelines [10, 13, 25], and consists of, but is not limited to:Therapeutic (custom-made) footwear that is evaluated every 3 to 6 months by a medical specialist and/ or professional (e.g., orthotist, podiatrist). Footwear can include custom-made shoes, semi-custom-made shoes, and orthopedic appliances to footwear or podiatric insolesPatient education that is provided by verbal and/ or written information by physician, podiatrist or the investigator during the baseline visit. Information addresses ulcer etiology, risk factors for ulceration, and self-care practicesOnce every 3–6 months multidisciplinary foot care and screening and/ or once every 1–3 months preventative foot care and screening by a podiatrist and/ or diabetes pedicure

Participants are advised to contact their podiatrist if they identify an area of concern.

### Enhanced therapy

Enhanced therapy consists of:Usual care (see above), *and*At-home daily measurement of foot temperatures with an infrared thermometer on six predefined plantar regions on each foot, plus an additional one or two locations based on participants’ ulcer history or pre-ulcer status, if indicated and if different from the predefined locations

Using an infrared thermometer (TempTouch®, Diabetica Solutions, San Antonio, TX, USA) [15–17], skin temperature is measured at six predefined locations on the plantar surface of each foot: hallux, second and third toes, first, third, and fifth metatarsal heads. In addition, based on the participants’ ulcer history or pre-ulcer status, a maximum of two plantar foot regions can be added to the six predefined locations. For example, a midfoot region could be added for a person with a Charcot deformity.

The foot temperature will be measured once per day at both feet, per instruction in the morning directly after waking up. To standardize measurements, a video for the correct use of the thermometer has been developed and is shown to the participants in the enhanced therapy group during the baseline visit. To facilitate measurements and to facilitate adherence to measuring foot temperatures, the participant is advised to place the thermometer, logbook, and a pen on their bedside table. The participant will record each temperature value in a logbook. The participant will be asked to return completed logbooks to the coordinating study center (Academical Medical Center) every 4 weeks. Participants will receive once in 2 weeks a text reminder on their mobile phone to stimulate adherence in temperature monitoring and to remind them to decrease their ambulatory status if skin temperature in a region is > 2.2 °C compared to the corresponding region on the contralateral foot for two consecutive days.

If skin temperature measured in a region is > 2.2 °C compared to the corresponding region on the contralateral foot for two consecutive days, the participant is instructed to contact their podiatrist. The podiatrist will ask them about any swelling, change in color, change in structure, or drainage present at the high-temperature location. Based on these outcomes, further diagnosis at the podiatrist’s office may take place. In any case, the participant will be asked to decrease ambulatory activity with approximately 50% until the temperatures normalize (≤ 2.2 °C temperature difference) [15–17]. If the temperature difference exceeds 4 °C, or if temperatures do not normalize and are abnormal for four consecutive days, the participant is advised to arrange to be seen immediately by their podiatrist. If pre-signs of a foot ulcer are identified by the podiatrist, necessary precautions will be taken. This may include further offloading with therapeutic footwear or insoles, orthoses, felted foam or debridement. If needed, direct referral for treatment to specialized multidisciplinary care will take place. This may involve, among other things, immobilization of the foot.

During the first 2 weeks after randomization, patients are instructed to contact their local study investigator in case of abnormal (> 2.2 °C) temperature differences at the predefined regions on two or more consecutive days. These measurements may reveal structural temperature differences (> 2.2 °C) between the regions of interest of both feet without any symptoms or signs of inflammation or ulceration present (e.g., due to mild to moderate unilateral peripheral arterial disease). In these cases an individually calculated threshold temperature will be used based on the mean temperature difference between the left and right foot measured in the first 2 weeks after randomization.

Participants who are unable to measure skin temperature at the standard predefined regions due to amputation will measure at an alternative region to replace the amputated site according to a specifically designed amputation protocol (Table 1).

**Table 1 Tab1:** Amputation protocol

Amputation site	Alternative region for measurement on the ipsilateral foot	Region(s) for comparison on the contralateral foot
Hallux	MTH 1 or 2nd toe^a^	Hallux
2nd toe	3rd toe	2nd toe
3rd toe	2nd or 4th toe^a^	3rd toe
Hallux and (trans)metatarsal I	- Most distal plantar part of the amputation site or 2nd toe^a^	- Hallux
	- Most distal plantar part of the amputation site	- MTH 1
2nd toe and (trans)metatarsal II	3rd toe	2nd toe
3rd toe and (trans)metatarsal III	- 4th toe	- 3rd toe
	- Most distal plantar part of the amputation site	- MTH 3
5th toe and (trans)metatarsal V	Most distal plantar part of the amputation site	MTH 5
Transmetatarsal amputation of the forefoot	Most distal plantar part of the amputation site at the base of the 1st, 3rd, and 5th metatarsals	MTH 1, 3, and 5^b^
Amputation of the forefoot through the Lisfranc joint	The plantar site of the 1st cuneiform bone, 3rd cuneiform bone, and the cuboid bone	MTH 1, 3, and 5^b^
Amputation of the forefoot through the Chopart joint	Most distal plantar part of the amputation site: medial, mid, and lateral	MTH 1, 3, and 5^b^

^a^Based on temperature values in the first 2 weeks, the investigator chooses the alternative region

^b^In case of a transmetatarsal amputation of the forefoot, or a more proximal amputation, no alternative region to measure for the hallux, 2nd and 3rd toes can be identified. In these cases, the measured temperatures of these regions in the intact foot are compared with the mean temperature of these regions measured in the first 2 weeks of temperature monitoring, using the same foot as reference. This is comparable to the protocol used for participants with a unilateral transtibial amputation. For further explanation, see the text

If participants have a transtibial or more proximal amputation, plantar foot temperatures at the predefinedregions of the intact foot will be compared to a calculated mean temperature of the same regions as obtained during the first 2 weeks of measurement after randomization. The investigator calculates the mean temperature for each region over the first 2 weeks, enters these as reference in the logbooks of the participant and sends the logbooks to the participant. Starting in the third week, participants compare their daily temperatures with these new reference temperatures. The same threshold temperature (> 2.2 °C) applies.

### Outcomes

The primary outcomes in this study are the cost (savings) per patient without a foot ulcer (i.e., cost-effectiveness) and per QALY gained (i.e., cost-utility). The primary clinical outcome is the proportion of participants with a recurrent foot ulcer on the plantar foot, apical surfaces of the toes, interdigital spaces or medial and lateral forefoot surfaces during 18-month follow-up. A foot ulcer is defined as a cutaneous erosion through the dermis without reference to time present [22, 23]. Endpoints in the study are either a foot ulcer, or 18 months of follow-up.

Secondary outcomes are the costs of therapy and of ulcer treatment, adherence to at-home foot temperature monitoring, and a multivariate risk score for ulcer recurrence.

### Study procedures

The study investigators will obtain informed consent and will perform all study measurements, during baseline and the 3-month semi-structured interviews with participants by phone.

#### Baseline assessment

After providing informed consent, participants will undergo a baseline assessment at their study center to confirm definitive eligibility for inclusion in the study. The following characteristics will be obtained during the baseline visit:Demographic information and disease-related characteristics (e.g., diabetes duration and control, presence of complications, ulcer history, footwear use, etc.);Peripheral neuropathy assessment:Presence of neuropathy will be assessed by measuring the loss of protective sensation by using the 10-g (5.07) Semmes-Weinstein monofilament at the plantar surface of the hallux and the first and fifth metatarsal heads of both feet [10]. Neuropathy is defined when the monofilament is not felt on two or more locations [22]A 128-Hz tuning fork held on the apex of the great toe [10]. Neuropathy is defined when the participant indicates not feeling the vibration [22]Peripheral vascular assessment by palpation of the dorsalis pedis and posterior tibial pulses of both feet, according to the PEDIS classification system [23]. If pulses are not palpable, additional assessment of peripheral vascular status will be done by measuring toe pressures or the participant’s medical record is checked for their vascular statusPresence of foot deformity will be assessed clinically. These include hammer/ claw toes, prominent metatarsal heads, hallux valgus, pes planus, pes cavus, Charcot deformity, and any amputation. A participant’s feet will be classified into one of four categories according to the severity of deformity present: no deformity, mild deformity, moderate deformity, and severe deformity [24]

If definitive eligibility has been confirmed, photographs of the plantar and dorsal surfaces of both feet will be taken according to a standardized protocol [24], and health-related quality of life will be assessed by using the 36-Item Short Form Health Survey (SF-36) and the 3-Level EuroQol Quality of Life Scale (EQ-5D-3 L) questionnaires.

#### Ulceration

If the participant, treating physician, podiatrist or pedicure identifies an ulcer between regular study visits, they are instructed to inform the diabetic foot team or podiatrist immediately, and have photographs taken of the foot. The podiatrist will take photographs of the wound, debride the wound if required to assess outcome, classify the ulcer using the University of Texas system and the PEDIS classification system, and again take photographs of the lesion after debridement using a standardized protocol and enter all data in an outcome Case Report Form (CRF) [23, 26]. This information will be sent to the investigator, who will upload all information anonymously to a web-based environment for ulcer outcome assessment by a panel of, minimally, three blinded and independently operating foot care specialists that will determine the definitive outcome [24].

#### Health-related quality of life and costs

For the cost-effectiveness and cost-utility analysis, the following data will be collected at 3-monthly intervals:Health-related quality of life will be assessed by asking participants to complete the EQ-5D-3 L questionnaire. These questionnaires will be sent to the participant’s home and returned after completion in an enclosed return-envelopeAt the same time-interval of 3 months, or in case a foot ulcer develops at monthly intervals, the participant is asked to complete the study-specified versions of the Institute for Medical Technology Assessment (iMTA) Productivity Cost Questionnaire (iPCQ) and the iMTA Medical Consumption Questionnaire (iMCQ) [27] to gather volume data on productivity loss, out-of-hospital use of health care resources (e.g., podiatrist, pedicure), and out-of-pocket expensesUse of intramural health care resources during the study will be obtained from the participants’ medical status

#### Process evaluation

At 3-monthly intervals, the investigator will contact the participant by phone to conduct a process evaluation of the intervention. Intervention group participants will be asked in a semi-structured interview about their experiences with at-home temperature monitoring. All participants will also be asked about contacts with health care professionals and any foot problems encountered in the previous 3-month period to crosscheck for the completed iPCQ and iMCQ questionnaires and about any lesion that may have developed.

### Data management

The participants will be coded by the number of the participating center (two digits) followed by the number of the participant (three digits). All information referring to the patients will be saved in a locked record office or on a computer with password security. Only the investigators have access to this study information. Name and date of birth of the participants will only be recorded on the informed consent form, which will be kept in a locked cupboard with the lead investigator per center, separate from the digital data and without a possibility to trace the data. All study data will be entered anonymized in an electronic database OpenClinica®. All study information will be saved for at least 15 years after the study has ended.

### Monitoring

Given the pragmatic nature of the intervention and the very low, negligible, risk for the participants in the study, an independent Data Safety and Monitoring Board has not been established. The investigators are responsible for procedures of data monitoring. To facilitate compliance with Good Clinical Practice guidelines, the investigator will permit study-related monitoring, audits, and inspections by authorized organizations. Aspects that will be monitored may include: inclusion rate; trial master file; informed consent progress; inclusion and exclusion criteria; source data verification; safety reporting; investigational product; trial procedures; and closing and reporting. Currently, the DIATEMP trial is monitored internally by the Academic Medical Center Amsterdam, VU Medical Center and the Maastricht University Medical Center. The role of the data monitor is to review study documentation, CRFs, and informed consents.

### Withdrawal of participants

Participants can withdraw from participation in the study at any time for any reason if they wish to do so, and without any consequences for their normal care. The physician can decide to withdraw a participant from the study in case of urgent medical reasons. After withdrawal from the study, information on ulcer outcome at 18 months will be obtained from the participant’s medical record if the participant consents to this procedure. Ulcer outcome data from participants who die during the study will be based on outcome at the moment of death (last observation carried forward).

### Serious adverse events (SAEs)

Any SAE that occurs during the study will be reported by the principal investigator to the accredited Medical Research Ethics Committee (METC) that approved the protocol within 15 days of when the principal investigator has been informed about the serious adverse event (within 7 days if death is the SAE).

### Statistical analysis

Statistical analysis will be performed after the last follow-up visit of the last participant in the study, and will be conducted using SPSS statistical software (IBM Corporation, Armonk, NY, USA). All tests will assess group effects, will be two-sided, and use *P* < 0.05 as significance level. All comparisons between groups are based on both an intention-to-treat and a per-protocol analysis.

Effectiveness of the intervention will be assessed using chi-square analysis. A competing risk analysis will be done to assess the difference by time to ulcer recurrence, with unrelated death as the competing risk and absence of ulcer at 18 months as censored observation.

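### The chi-square test for ulcer recurrence ignores the minimization factors, centre and gender; if either predicts ulceration, it is mildly conservative and gives up a little power

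*Protocol article*

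**What the plan says.** Randomization and blinding describes minimization with a random element and names its factors: "Randomization will be stratified according to participating center and gender". I read this as minimization with centre and gender as the two balancing factors. Study design lists seven hospitals, so there are up to 14 centre-by-gender cells.

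Statistical analysis gives the test for the primary clinical outcome: "Effectiveness of the intervention will be assessed using chi-square analysis". It names no stratified test and no covariates for this comparison, and none for the competing-risk analysis of time to recurrence. The multivariate risk score under Outcomes is a secondary outcome, not an adjusted comparison of the arms.

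Sample size calculation expects that "44% of participants will develop a recurrent foot ulcer during 18 months" under usual care, against "28.6% of participants in the enhanced therapy group will develop a recurrent foot ulcer in 18 months", and concludes that "304 eligible participants are required and will be randomly assigned".

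**The concern.** Minimization forces the arms to be alike in centre and gender. Variation in ulcer risk due to those factors is therefore largely removed from the difference between arms. The plain chi-square takes its standard error from the total outcome variance, as if that balance had arisen by chance. If either factor is prognostic, the standard error is too large: the test rejects a true null less often than 5% of the time and detects a real effect less often than it could.

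At stake is efficiency. The designers judged the two factors important enough to balance on, and the planned analysis does not collect the benefit. An adjusted analysis needs no extra patients.

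**Working it through.** **1. Reproducing the plan's figure.** Inputs, all from Sample size calculation:
- level and power (in %): "With α = 0.05 (two-sided), power 80"
- recurrence p1 = 0.44 and p2 = 0.286; 1 − 0.286/0.44 = 0.35, which agrees with "this represents a 35% effect size"; d = 0.154
- no inflation for dropout: "intention-to-treat analysis in which clinical outcome data from all included patients will be assessed"
- 1:1 allocation is my assumption, as the ratio is not stated.

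Two-proportion test, pooled variance, no continuity correction, p̄ = 0.363:

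n per arm = [1.960·√(2·0.363·0.637) + 0.842·√(0.44·0.56 + 0.286·0.714)]² / 0.154² = (1.333 + 0.565)² / 0.0237 ≈ 151.9, so 152.

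The total is 304, as stated, and power at 152 per arm is 80.03%. The sample size was built on the unadjusted test.

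**2. Analytic approximation.** Let the balanced factors explain a share R² of the outcome variance. The true variance of the difference shrinks by 1 − R², but the chi-square does not use this. With se0 = √(2·0.363·0.637/152) = 0.0552 and se1 = √(0.4506/152) = 0.0544:
- true level of the chi-square = 2·[1 − Φ(1.960/√(1 − R²))]
- power, chi-square = Φ[(0.154 − 1.960·se0) / (se1·√(1 − R²))]
- power, adjusted = Φ[(0.154 − 1.960·se0·√(1 − R²)) / (se1·√(1 − R²))]

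| R² | Level, chi-square | Power, chi-square | Power, adjusted |
|---|---|---|---|
| 0% | 5.0% | 80.0% | 80.0% |
| 2% | 4.8% | 80.3% | 80.8% |
| 5% | 4.4% | 80.6% | 82.0% |
| 10% | 3.9% | 81.3% | 84.0% |

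**3. Simulation of minimization.** There were 4,000 trials per setting, with N = 304 and seven centres. Overall rates were calibrated to 44% and 28.6%. Assumptions: each patient is assigned to the better-balancing arm with probability 0.8, 70% of patients are of one gender, and centres hold 6% to 25% of patients. The adjusted analysis is a linear model with arm, centre and gender. CMH is the Cochran-Mantel-Haenszel test over 14 strata.

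| Centre SD (log-odds), gender OR | Variance explained | Level, chi-square | Power: chi-square / CMH / adjusted |
|---|---|---|---|
| 0, 1.0 | 0% | 5.2% | 79.8 / 78.8 / 79.7% |
| 0.3, 1.3 | about 2% | 4.3% | 80.2 / 80.0 / 80.6% |
| 0.5, 1.5 | about 5% | 4.3% | 80.7 / 81.3 / 82.0% |
| 0.8, 1.5 | about 11% | 3.5% | 81.9 / 84.1 / 84.9% |
| 1.0, 2.0 | about 16% | 3.1% | 82.4 / 85.9 / 86.7% |

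Monte Carlo error is about 0.3 points for level and 0.6 for power. The tests are run on the same simulated trials, so differences within a row are more precise than that.

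A second simulation at the same overall rates gave chi-square versus adjusted power of 80.2% vs 80.4% (no effect), 82.0% vs 82.5% (SD 0.3), 81.3% vs 83.0% (SD 0.5) and 81.4% vs 84.9% (SD 0.8, chi-square level 3.4%).

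For scale, centres one SD above and one SD below average differ by an odds ratio of exp(2 × 0.3) = 1.8, exp(2 × 0.5) = 2.7 and exp(2 × 0.8) = 5.0 respectively.

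**4. Why some simulations would show power below 80%.** With centre SD 0.8 and a gender log-odds of 0.4, suppose 44% and 28.6% are used as conditional rates, before centre and gender effects are averaged over. The overall rates then drift to about 44.8% and 31.0%, a difference of 13.8 points instead of 15.4. Power is 71.1% for the chi-square and 75.3% adjusted. The article gives its rates as proportions of participants, that is, overall rates. Calibrated to those, the same setting gives 82.1% and 85.3%.

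**The case against.** The best defence is that the chi-square matches the method behind the sample size, meets the planned power in every calibrated setting, and errs on the safe side. The gain from adjustment is under one point at SD 0.3, and the 3 to 4 point gain needs centre differences for which the article offers no evidence. The article is also a condensed account, and an analysis plan that is not shown may add an adjusted analysis. All of this stands as a limit on size. It does not remove the mismatch: the article itself names the test, and adjustment costs essentially nothing even when the factors are irrelevant.

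A reader might infer more than the article supports:
- **The trial is underpowered because of the test.** It is not. Power below 80% appears only when a smaller effect than the planned one is simulated (step 4).
- **Risk differs by centre, or the two added centres recruited under wider eligibility.** The Discussion reports two added centres and a longer ulcer-free window, but neither links the two nor gives their relative timing. No section reports risk by centre.
- **The confidence intervals are too wide.** None is specified for the clinical effect; the only 95% intervals are the bootstrap ones in Economic evaluation.
- **Leaving out time since healing is an error.** It is not a randomisation factor. The Discussion treats recent healing as a marker of higher risk, so it is a sensible covariate, but an optional one. Baseline assessment lists ulcer history without saying that a healing date is recorded.

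**Conclusion.** The point holds as a minor matter of efficiency. The named test ignores both minimization factors, and nothing else in the article makes up for it. If centre or gender is prognostic, the chi-square is mildly conservative. It forgoes about 0.5 to 2 power points at centre SD 0.3 to 0.5, and 3 to 4 points at SD 0.8, where its type I error is near 3.5%. What is forgone is power above the planned 80%, so the sample size of 304 is not in question and there is no excess of false positives. If neither factor is prognostic, nothing is lost.

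The direction follows from the design. The size rests on assumed centre and gender effects, 1:1 allocation, the assumed strength of the minimization and assumed centre sizes, none of which the article gives.

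**What to change.** Before outcomes are compared by arm:
- Make the primary clinical analysis a main-effects model with arm, centre and gender, for example logistic regression standardised to a risk difference and risk ratio with 95% confidence intervals. A main-effects model is preferable to a 14-stratum CMH test, which had about one point less power when the factors did not matter (78.8% vs 79.7%).
- Include centre and gender in the competing-risk model.
- Keep the chi-square as a supportive analysis.
- Optionally, prespecify time since ulcer healing, with a separate category for patients who qualify by Charcot disease alone, if the healing date is recorded.

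The cost is wording. Centre and gender are known for every patient because allocation uses them. At the planned rates about 0.363 × 304 ≈ 110 patients would have an ulcer, against eight model terms (arm, six for centre, one for gender), so the model is affordable. A rule for pooling very small centres should be set in advance. If an analysis plan already adjusts for these factors, the article's statement of the test should be reconciled with it.
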